## Abstract

**Background:**

Adolescent obesity epidemic is one of the major health priorities as it tracks into adult life. There is widespread need for new creative strategies and lifestyle programs. This study was designed to investigate the possible impact of including peers on the weight management program and assess the long-run adherence to behaviour change, with a potential positive impact on body mass index, body composition, and physical activity. Peer influence is major at this age and it is expected that adolescents will be better motivated and engaged in the behaviour changes when they are accompanied by their friends.

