### Objective

The main objective of this project is the development, implementation and assessment of an adolescent obesity treatment programme, which will use PA and interactive sessions to promote skills for achieving weight control in a context of increased contact between the adolescents, peers and the team.

As such, the following objectives were defined:

1. To contribute to an effective weight management of adolescents, through reducing the BMI z-score and% Fat Mass (FM), increasing PA and reducing sedentary behaviour;

2. To analyse the effects of including peers and an increased exposure time of adolescents to PA and IS, on psychosocial health, eating habits, physical fitness and metabolic and inflammatory markers.

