### Subject withdrawal

The following will give rise to the withdrawal of participants:

•Attendance less than 75% of the IS or PA sessions;

•Acute illness implying non-compliance with the planned sessions;

To ensure that the participants comply with the assumptions, records will be kept of the attendance at the IS and PA sessions. Participants will not be substituted.

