### Data collection

The variables will be assessed according to Table 1.

**Table 1 T1:** Variables, measures and timing of the data collection

**Parameters**	**Assessed through…**	**When**
IS attendance	Attendance sheets	IS
Frequency of exercise	Training plans and attendance records	IS and Exercise sessions
PA	Pedometers (OMRON Walking Style II, HJ-113-E) PA records (7-Day Physical Activity Recall)	IS/Holiday Camps
PA and Sedentary behaviour	Accelerometers (Actigraph GT3X)	0, 4, 8, 12, 24, 36 months
BMI	Weight (OMRON BF-500) SECA height stadiometer	
% Fat mass	Bioimpedance (OMRON BF-500)	
Body composition	Dual-energy X-ray absorptiometry, DEXA (QDR-1500; Hologic, Waltham, MA)	
Physical fitness	FITNESSGRAM test battery	
Caloric intake	Food records (4-day recall)	
Quality of Life	Impact of Weight on Quality of Life – Kids (IWQOL-kids) Kidscreen-27	
Well-being	Rosenberg Self-Esteem Scale (RSES) Body Image Assessment Questionnaire (BIA) Body Shape Questionnaire (BSQ)	
Peers	Perceptions of Parents Scales (POPS) – adapted to peers Self-Perception Profile for Adolescents (SPPA) – Social Acceptance Scales and “Best Friends”	
Self-regulation variables	Treatment Self-Regulation Scale (TRS) Locus of Causality for Exercise (LCE) Weigh Management Self-efficacy (WMSE) Behavioural Regulation in Exercise Questionnaire (BREQ-2) The Psychological Need Satisfaction in Exercise Scale (PNSE)	

Notes: IS – Interactive sessions; PA – Physical Activity.

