### Outcomes

Taking into account the recommendations of Barlow [57] and following analysis of the results of two recent meta-analyses [1,5], the following outcomes were defined (see Table 2).

**Table 2 T2:** Study outcomes

**Variables**	**Goal**
BMI	5% z-score reduction
Body composition	5% reduction of percent fat mass
Psychosocial	Improvements of 0.5 standard deviation
PA time	Increase moderate/vigorous PA (≥60 min per day)
Sedentary behaviour	≤ 90 minutes per day
Caloric intake	1000-1500 Kcal daily intake

Note: PA – Physical Activity.

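### Adherence is an announced aim with no defined outcome, and the 75% attendance rules would confine any between-arm adherence comparison to good attenders

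*Protocol article*

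**What the plan says.** **Aim.** The Abstract (Background) gives two purposes: the impact of including peers, and to "assess the long-run adherence to behaviour change". It expects that "adolescents will be better motivated and engaged in the behaviour changes when they are accompanied by their friends".

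**Objectives and outcomes.** Objective 1 is effective weight management "through reducing the BMI z-score and% Fat Mass (FM), increasing PA and reducing sedentary behaviour". Objective 2 covers psychosocial health, eating habits, fitness and markers. Table 2 has six rows: BMI, body composition, psychosocial, PA time, sedentary behaviour and caloric intake. Neither place names adherence, attendance or retention.

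**Attendance.** Table 1 lists attendance at the interactive sessions (IS), and frequency of exercise taken from "Training plans and attendance records". Under Subject withdrawal, "Attendance less than 75% of the IS or PA sessions" leads to withdrawal, and "records will be kept of the attendance at the IS and PA sessions" so that compliance can be checked. Discontinuation removes from the analysis anyone who misses more than a quarter of sessions.

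**Long-run data.** Table 1 schedules accelerometer PA and sedentary behaviour at 0, 4, 8, 12, 24 and 36 months. The programme lasts 12 months.

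**Analysis.** Data analysis plans repeated measures ANOVA, structural equation and/or mediation models, and intention-to-treat with last observation carried forward.

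**The concern.** According to the Intervention section, the chosen peer is the only difference between the arms. The Abstract expects that peer to act through motivation and engagement. If it does, part of the effect will show in who keeps coming and who drops below 75%. The plan uses that same quantity, measured after the intervention has begun and possibly affected by the arm, to decide who stays and who is analysed.

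This has two consequences. Any look at attendance among those retained starts at 75% in both arms. The long-run behavioural comparison is made between groups that were selected to different degrees: if peers help, the comparison arm loses more of its less engaged members, and those who remain resemble the peer arm more closely than the enrolled groups did. A stated purpose of the study would then have no outcome set in advance and a distorted comparison behind it.

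**Working it through.** **1. The plan's own figure.** Sample size calculations gives power 0.90 at N = 134 for an effect of 0.25, falling to 0.82 after 25% attrition. The metric is not stated. One standard reading is a between-group effect in repeated-measures ANOVA with f = 0.25, two measurements, correlation 0.5 and equal groups, all assumed. Then λ = 134 × 0.0625 × 2 / 1.5 = 11.2, giving power 0.91; at N = 101, λ = 8.4 and power is 0.82. The figure is roughly reproduced. It concerns the primary outcomes, and this point does not rest on it.

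**2. Both rules set the same cut.** Missing more than 25% is attending less than 75%. One rule withdraws these adolescents and the other removes them from the analysis.

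**3. Effect of the cut on attendance.** The documents give no attendance figures, so these are assumptions: X normal with mean μ and SD 15, capped at 100. With a = (75 − μ)/15 and b = (100 − μ)/15:

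- mean in all enrolled = μΦ(b) − 15φ(b) + 100[1 − Φ(b)]
- share reaching 75% = 1 − Φ(a)
- mean among those kept = {μ[Φ(b) − Φ(a)] + 15[φ(a) − φ(b)] + 100[1 − Φ(b)]} / [1 − Φ(a)]

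| Nominal μ, peer / comparison | Mean, all enrolled | Difference | Share ≥75% | Mean, those kept | Difference |
|---|---|---|---|---|---|
| 80 / 70 | 79.4 / 69.9 | 9.5 | 0.63 / 0.37 | 88.0 / 85.0 | 3.0 |
| 78 / 73 | 77.5 / 72.8 | 4.7 | 0.58 / 0.45 | 87.3 / 85.8 | 1.5 |
| 88 / 78 | 86.2 / 77.5 | 8.7 | 0.81 / 0.58 | 90.9 / 87.3 | 3.6 |

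Share below 75% overall:
- 80/70: (99 × 0.369 + 35 × 0.631)/134 = 44%
- 78/73: (99 × 0.421 + 35 × 0.553)/134 = 46%
- 88/78: (99 × 0.193 + 35 × 0.421)/134 = 25%, which matches the protocol's expected attrition

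The surviving difference is about 32% of the true one in the first two rows and 41% in the third.

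**4. Carry-over to the behavioural outcomes.** Selection raises mean attendance by 15.1 points in the comparison arm and 8.6 in the peer arm for 80/70. The excess is 6.5 points, or 6.5/15 = 0.43 SD. For 88/78 it is 8.7 − 3.6 = 5.1 points, or 0.34 SD. If a behaviour such as MVPA correlates r with attendance within arms, its contrast shifts by about r times this. With r assumed at 0.3 to 0.5, that is 0.10 to 0.22 SD against the peer arm. If r is zero there is no shift.

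**5. What a comparison in all enrolled could show (99 v 35).**

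- Mean attendance: SE = 15√(1/99 + 1/35) = 2.95. Power = Φ(difference/2.95 − 1.96): 0.90 for 9.5 points, 0.84 for 8.7 and 0.36 for 4.7.
- Proportion reaching 75% (two-proportion normal test, pooled variance under the null): 0.77 for 63% v 37% and 0.27 for 58% v 45%. If 75% of the comparison arm reach the threshold, power is 0.10, 0.28, 0.58 and 0.86 against 80%, 85%, 90% and 95%.
- Precision at 85% v 75%: SE = √(0.85 × 0.15/99 + 0.75 × 0.25/35) = 0.0815, so the 95% interval is about ±16 points.

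**The case against.** The strongest reply is that the aim is adherence to behaviour change and not attendance at sessions. PA, sedentary time and intake are Table 2 outcomes, accelerometry runs to month 36, and a repeated-measures comparison is planned. Motivation and peer support are measured as mediators, with mediation models to follow. On that view only a label is missing, and how attendance is summarised can be left to a fuller document. Most of this stands. It does not meet the selection problem: if removal applies, the behavioural and mediation analyses are run on those who attended.

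A reader might infer that attendance serves only for withdrawal and that the trial cannot say whether peers improve adherence. The documents do not support either. Table 1 lists attendance and exercise frequency as study variables, and the number in each arm falling below 75% is itself a contrast that could be reported.

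The 80/70 and 78/73 scenarios put about 44% and 46% below the threshold against the 25% attrition that the protocol expects. That criticism is fair, and the 88/78 row answers it: the shrinkage is milder but still more than half.

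The intention-to-treat sentence could also be read as keeping low attenders in. It conflicts with the removal rule, and that conflict is a matter of its own. If measurement stops at withdrawal, which the article does not state, carrying forward would place an in-programme value at months 24 and 36. That value would not be long-run information.

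**Conclusion.** The point holds in a limited form. Adherence is a stated purpose without a defined outcome, and the 75% rules would restrict the relevant comparisons to adolescents who attended well. That much follows from reading the sections together.

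The size depends on assumption. With an SD of 15 points, between three-fifths and two-thirds of a true attendance difference disappears among those kept. The effect on the behavioural outcomes depends on their correlation with attendance, which the documents do not give.

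Even in all enrolled adolescents the comparison may be imprecise, with power from about 0.1 to 0.9. Allocation by whether a peer was available limits causal reading of any difference. This is worth correcting as a secondary matter: the data needed are already scheduled.

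**What to change.** Name adherence as a secondary between-arm outcome in Table 2, analysed in all enrolled adolescents:

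1. **Programme adherence.** Report by arm the proportion attending at least 75% of scheduled IS and PA sessions, and the percentage attended up to withdrawal or month 12. Ending the count at withdrawal keeps sessions missed because the protocol withdrew the adolescent from being scored as non-adherence. Give reasons for withdrawal by arm.
2. **Long-run adherence.** State that the planned accelerometer comparisons of MVPA and sedentary time at months 24 and 36 are the measure of long-run adherence. Keep low attenders in them, and report retention by arm at months 12, 24 and 36.
3. **Reporting.** Give estimates with 95% confidence intervals, not a confirmatory test, and note that allocation was by availability of a peer.

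The removal rule under Discontinuation and the intention-to-treat sentence under Data analysis must be reconciled for item 2 to work. Whether an adolescent continues in the sessions is a separate question that this change leaves alone.

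The cost is one more secondary outcome and a few analyses of scheduled data. No visit is added to the schedule and the sample size is unchanged, but low attenders have to be followed at the visits already planned.

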**Methods/design:**

The study is a non-randomised, non-blinded controlled trial, including two groups: 1) Comparison group (n = 35), which will receive a 12 month standard treatment at the hospital setting plus a weekly interactive and physical activity session; 2) Experimental group (n = 99), which will receive the standardized treatment at the hospital plus a weekly session together with a peer of their choice. The sample size calculations for the primary outcomes showed that we will have power to detect effect sizes of 0.25. Measures include: a) Dual-energy x-ray absorptiometry (for body composition assessment); b) Anthropometric evaluations; c) Assessment of physical activity levels by accelerometers; d) Psychosocial mediators (motivation and peer support) assessed with a package of psychometric questionnaires; and e) Outcomes (quality of life and well-being).

**Discussion:**

Adolescence is a crucial period for the development of a healthy lifestyle, especially among those who reach this age with an obesity condition. Obesity management programs directed to adolescents are often an adopted version of programs developed for children, most of them with a strong focus on the family, or an adopted version of adult programs, not recognizing the specificities of this age group. This study is designed taking into account the unique characteristics of this life-cycle stage, with the main objective of testing an innovative treatment for adolescent obesity.

**Trial registration:**

This trial is registered in the clinicaltrials.gov with the number NCT02024061

## Background

Paediatric overweight and obesity have reached epidemic proportions in most industrialised countries [1]. In Portugal, a Southern European country with a traditional Mediterranean diet, the prevalence of overweight adolescents is among the highest in Europe. In a recent study [2], using a representative sample of Portuguese young people (22048 adolescents) aged between 10 and 18 years, there was an estimated prevalence of overweight and obesity of 23.1% and 9.6%, among girls and of 20.4% and 10.3% among boys, respectively. It was also seen that the prevalence of overweight and obesity decreases with age for boys and for girls from 13 to 18.

It is of the utmost importance to work on prevention to deal with this epidemic [3,4]. However, efforts must also be made to treat those young people who are already overweight [1,5]. There are several facts to support this need, in particular because adolescent obesity: a) has a significant impact on physical and psychosocial health [6]; b) is an independent risk factor for adult obesity [7]; c) is an independent risk factor for mortality in adults, perhaps more powerful than adult obesity itself [8]; and d) is a major threat to the sustained increase of life expectancy [9].

The psychosocial consequences represent the most prevalent co-morbidities associated with obesity [10]. Obese young people have low self-esteem (SE) and a reduced quality of life (QoL), mainly associated with their perceptions of physical appearance, athletic skills and social functioning [6]. There seems to be a dose–response association between the Body Mass Index (BMI) and a worse health related QoL in such a way that severely obese people have significantly higher values than those seen in people with a less severe degree of obesity [11]. Moreover, obese individuals show higher levels of body dissatisfaction [12] and higher levels of depression [13]. Body Image (BI) has been consistently identified as a protection factor against the development of risky behaviour associated with obesity [14].

Obese adolescents with low levels of self-esteem have shown significantly higher levels of sadness, loneliness and anxiety and are more susceptible to engage in experimental/risky behaviours [9], such as smoking or drinking [15]. Fonseca and Matos [16] showed that overweight adolescents find it harder to make new friends when compared with their peers who are not overweight.

The questions of physical fitness associated with health are increasingly determinant in the way young people negotiate their daily lives and prepare for the future. In adolescents, a low cardiorespiratory fitness value is closely associated with an increased risk for developing cardiovascular diseases, regardless of country, age or gender [17]. To avoid the accumulation of risk factors for the development of cardiovascular diseases, the *European Youth Heart Study*[18] recommends that young people should perform more than one hour of moderate to vigorous physical activity (MVPA) per day. It has further been identified that higher amounts of MVPA hours are associated with a decrease in cardiometabolic risk factors [19]. However, an increase in physical activity (PA) alone does not solve the problem, as a decrease in sedentary behaviours (e.g. screen time) is crucial metabolic risk and adiposity control [20].

The health of individuals does not come only from their biology and/or individual actions but also from the biology and actions of those around them [21]. This issue is particularly relevant in adolescence as friends play an essential role in the developmental process, through the emotional support that is associated with social affection. Very often, peers are referred to as a barrier to regular PA and healthy diet [22]. More studies are needed to better understand these reciprocal influences, in order to be able to deal in a more effective way with the psychosocial factors negatively impacting the life of the obese adolescent [23]. Interventions that are intended to improve self-efficacy and social functioning in young people can bring specific benefits to obese adolescents [24]. However, and despite different authors e.g. [25], having suggested that an increase support from peers in contexts of PA implementation may constitute a viable way of promoting active lifestyles among young people, this area has still not been much studied.

Although the literature consistently points out the direction for solving the problem, it has generally not been possible to directly and effectively influence PA [26]. Interventions using mediators have shown effective results in changing behaviour in the short term and there is increasing evidence that this approach may have long-term effects [27]. The role of self-efficacy has been clearly pointed to as a mediator in the relationship between the intervention and PA [28]. Recently, Rhodes and Pfaeffli [29], in a wide-reaching review, suggested that changes in the structure of self-regulation might have a greater mediator effect on changing behaviour relative to PA.

Our program, named **T**ratamento da **O**besidade **P**ediátrica (TOP), standing for Paediatric Obesity Treatment, has been implemented in 2004, and is the result of the cooperation between the Paediatric Obesity Clinic, Department of Paediatrics, at Hospital de Santa Maria (HSM) and the Faculty of Physical Education and Sport at Universidade Lusófona (UL) in Lisbon. This initiative gave rise to an innovative, yet sustained programme where several disciplines including PA specialists are simultaneously present in the Clinic, making it possible that adolescents receive integrated medical, nutritional and PA care on the same day. Respecting the most recent recommendations [30], we use behaviour modifying techniques aimed not only at the adolescents but also at their families and peers, using techniques based on the Self Determination Theory (SDT) and Motivational Interviewing (MI) [31] within a treatment protocol that has been presented at the Society for Adolescent Health and Medicine [32]. Based on our previous experience and on recent literature, it was theorised that to provide better care it would be necessary: a) more extensive and frequent contact with the treatment team and b) the inclusion of peers to assist in the weight control tasks. The literature shows that an adolescent’s health behaviour is associated with that of their peers [23], through social contagion [33,34] mechanisms. The reasoning behind the design of this project is the belief that providing regular PA, interactive sessions (IS) [35] and specific moments of concentrated intervention – holiday camps [36], would offer the right context for both reaching a more extensive contact with the treatment team and allow for the inclusion of peers in the treatment. This intervention is grounded on the rationale presented and the health behaviour modification model, based on the Self-Determination Theory - SDT [37]. The team believes that this interaction between PA, positive psychological effects and reduction in BMI will lead to an increase in the perceived well-being of adolescents, which in turn will reinforce health behaviour, as has been seen with adults [38].

### Objective

The main objective of this project is the development, implementation and assessment of an adolescent obesity treatment programme, which will use PA and interactive sessions to promote skills for achieving weight control in a context of increased contact between the adolescents, peers and the team.

As such, the following objectives were defined:

1. To contribute to an effective weight management of adolescents, through reducing the BMI z-score and% Fat Mass (FM), increasing PA and reducing sedentary behaviour;

2. To analyse the effects of including peers and an increased exposure time of adolescents to PA and IS, on psychosocial health, eating habits, physical fitness and metabolic and inflammatory markers.

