### Eligibility criteria

Inclusion Criteria: Obese adolescents with a BMI greater than or equal to the 95^th^ percentile [39], aged between 14 and 17, with Caucasian origin, agreeing with the commitment.

Exclusion criteria: a) cognitive impairment; b) pregnancy; c) serious illnesses; d) other factors with contraindication for regular PA.

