### Intervention

The study comprises an experimental group and a standard treatment group. The intervention will be similar in both groups with the exception that in the experimental group every adolescent will be escorted by a peer of their choice at every moment of the intervention (IS, PA sessions and holiday camps). The multidisciplinary team is made up of physical activity specialists, nutritionists/dieticians, psychologists and paediatricians, all of them with previous training in adolescent obesity, resulting from their involvement in the Paediatric Obesity Clinic at HSM.

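### Both groups receive the programme, so the trial can estimate only the added effect of the own peer; before-after change and the Table 2 goals cannot show that the programme or its exposure time works

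*Protocol article*

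**What the plan says.** The Objective section of the protocol article gives the main aim as the "development, implementation and assessment of an adolescent obesity treatment programme". Objective 1 is "To contribute to an effective weight management of adolescents, through reducing the BMI z-score and% Fat Mass (FM"), together with more physical activity and less sedentary time. Objective 2 is to analyse the effects of including peers and of longer exposure to physical activity and interactive sessions.

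Study design and setting gives both groups standard clinic care plus the 12-month programme of weekly sessions and camps. Allocation depends on whether the adolescent has a chosen peer. The Intervention section says: "The intervention will be similar in both groups with the exception that in the experimental group every adolescent will be escorted by a peer". That section also calls the comparison arm a standard treatment group. Interactive sessions confirms that content is identical and that the peer is the differential factor.

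Table 2 (Outcomes) lists goals that include "5% z-score reduction" and "5% reduction of percent fat mass". Data analysis plans a repeated-measures ANOVA for the intervention's impact and does not name the contrast.

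Eligibility criteria admits adolescents "aged between 14 and 17", and sets the BMI threshold as "Obese adolescents with a BMI greater than or equal to the 95"th percentile.

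**The concern.** The stated aim and the design answer different questions. The aim is to assess a programme and, in objective 2, the amount of exposure to it. The design varies neither, because no group goes without the programme and the sessions offered are the same in both groups. What varies is the peer.

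If both groups improve by a similar amount, these data support only the statement that no added effect of the own peer was seen. With objective 1 as worded, fixed percentage goals in Table 2 and no contrast named in Data analysis, the same result could be reported as an effective programme. The label standard treatment group adds to the risk: a reader could take a group difference as programme versus usual clinic care. An analysis plan cannot repair this, since no analysis of these two arms alone separates a programme effect from what would have happened without the programme.

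**Working it through.** **1. The plan's own figure.** Sample size calculations states power 0.90 at N = 134 for an effect size of 0.25 (two-sided 0.05), falling to 0.82 with 25% attrition. The effect-size metric and the test are not named. I assumed Cohen's f = 0.25, two equal groups, m = 2 measurements and within-person correlation r = 0.5, and tested the between-groups factor of a repeated-measures ANOVA with a noncentral F:

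- noncentrality = N × f² × m / (1 + (m − 1) × r)
- N = 134: 134 × 0.0625 × 2 / 1.5 = 11.17, power 0.913
- N = 100 (134 × 0.75 = 100.5): 100 × 0.0625 × 2 / 1.5 = 8.33, power 0.816

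Both are within 2 points of the stated values. The group-by-time interaction under the same settings gives 1.000 and 0.999, which does not match. So the stated power is consistent with a comparison between groups, that is, with the peer question. This is suggestive only, because m, r and equal groups are my assumptions. With the planned 99:35 split and a standardised difference of 0.5, the same model gives 0.83 and 0.71. The sample size is not the point at issue here.

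**2. What each question needs and what the arms supply.**

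| Question in the Objective section | Contrast needed | Available? |
|---|---|---|
| Does the programme reduce BMI z-score and % fat mass? | Programme versus no programme | No; both groups receive it |
| Does longer exposure to sessions help? | More versus less exposure | No; the same sessions are offered to both |
| Does including a peer help? | Peer versus no peer | Yes, but not randomised |

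Attendance may vary between individuals, but a comparison by attendance would be observational, not a comparison of the groups as designed.

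**3. How large the Table 2 BMI goal is.** The 95th percentile of a normal reference is z = 1.645. A 5% reduction is 0.05 × 1.645 = 0.082 z at the threshold and 0.05 × 3.0 = 0.15 z at an assumed baseline of 3.0. The mean of a standard normal truncated at 1.645 is 2.06, where 5% is 0.103 z.

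**4. Regression to the mean with no treatment effect and no age trend.** Let X be the baseline z-score and Y the follow-up z-score, standard bivariate normal with correlation rho, and select X ≥ 1.645. Then mean(Y) = rho × mean(X), so the mean proportional fall is 1 − rho. The share of individuals falling by at least 5% is from simulation (8 million draws, 400,641 selected).

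| rho | Mean fall | Share falling ≥ 5% |
|---|---|---|
| 0.99 | 1% | 28% |
| 0.97 | 3% | 44% |
| 0.95 | 5% | 50% |
| 0.93 | 7% | 54% |
| 0.90 | 10% | 59% |

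The documents do not give rho. The model also treats the measurement used for selection as the baseline; if baseline is measured again after screening, part of the regression occurs before it. The documents give no inputs for the same calculation on percent fat mass.

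**The case against.** The best defence is that this is a two-group controlled trial and should be read as one. The Abstract presents it as an investigation of including peers, and a natural course common to both groups cancels in a group-by-time comparison. Nothing in the text says objective 1 will be judged on before-after change. That is right for the peer question. It does not help the programme or exposure-time question, for which no between-group contrast exists. It is also fair that the contrast does not say nothing about the programme: the peer is one named component of it, and that component is tested.

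Three stronger readings might be inferred, and the documents do not support them.

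- *That obese adolescents are expected to improve with age.* The Background does say that "the prevalence of overweight and obesity decreases with age for boys and for girls from 13 to 18". This is survey prevalence by age; it follows no individuals, is not confined to the obese, and comes without a rate. The same article says that adolescent obesity tracks into adulthood. BMI z-score is already age-standardised, so ageing alone lowers it only if the adolescent falls relative to the reference. An individual decline is not established.
- *That Table 2 is a success rule.* Its column is headed Goal, it names no baseline or time point, and three of its six rows (activity, sedentary time, caloric intake) are absolute levels. No section says the programme will be declared effective if goals are met.
- *That the goals will be met without treatment.* At correlations of 0.97 or higher, regression to the mean alone gives a mean fall of 3% or less, short of 5%.

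What remains of the concern is the mismatch between the objectives and the arms, which none of these points removes.

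**Conclusion.** The point holds in a limited form. The arms as fixed can estimate the added effect of the own peer, subject to non-randomised allocation. They cannot estimate the effect of the programme or of exposure time, although the objectives name both. Falls from baseline, including attainment of the 5% goals, cannot be attributed to the programme, because selection at a high threshold can contribute to them. The size of that contribution is unknown. Under the truncated-normal assumption the mean fall runs from 1% to 10% for correlations from 0.99 to 0.90, and it equals the goal at 0.95. The conclusion about the arms does not depend on these figures; it follows from both groups receiving the same programme.

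**What to change.** 1. State that the trial's effect conclusion is the experimental versus comparison (group-by-time) contrast, interpreted as the added effect of the own peer.
2. State that before-after change and attainment of the Table 2 goals are descriptive and are not evidence that the programme or the exposure time is effective.
3. Reword objectives 1 and 2 to match: objective 1 as change described within groups and compared between them, objective 2 without an effect claim for exposure time.
4. In the Intervention section, replace the label standard treatment group with programme without own peer.
5. Optional: if the clinic holds suitable records of patients who had standard care without the weekly programme, report their z-score change beside both groups, labelled observational. The documents do not confirm that such records exist, and clinic patients would not match participants recruited through schools.

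Items 1 to 4 change only wording and leave the design, data collection and sample size as they are. The cost is a weaker claim about the programme.
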